### Treatments/interventions

2.6.

Since the intervention is planned as an add-on intervention, all participants will receive TAU in the clinic they are recruited from and are free to use any form of treatment that is offered to them. Due to the multicentre approach, TAU may differ between participants and will be recorded at T1 after the sleep intervention is completed. Potentially different therapeutic approaches in TAU will be included in exploratory data analysis.

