### Procedure and assessment

2.7.

After the recruitment procedure is completed, participants will provide written informed consent and are randomized to one of the two study conditions. Participants will then receive a link to an online questionnaire arranged in SoSciSurvey for baseline assessment (timepoint T0). Following baseline assessment, the intervention group will get access to the *somnio* app and receive dCBT-I for the subsequent 8 weeks whereas the control group will fill in an online sleep diary every day (link provided by email). Five weeks after the start of the intervention, participants will receive a phone call to encourage compliance and spot potential issues with the use of the app or sleep diary. Both groups will continue to participate in TAU of the respective clinic without any limitations. After the intervention phase (10 weeks post baseline), all participants will receive a link to a second online assessment (timepoint T1). Additionally, the researchers conducting the study will contact every participant for a phone interview around T1 to gather information about current medication, number, and content of trauma-related outpatient treatment sessions. Six months after baseline assessment, participants will be contacted again and asked to fill in a follow-up assessment (T2). All measures used for the assessments on different time points are listed in Table 2. At all assessments, participants have the possibility to pause filling out the questionnaires in case they become overwhelmed and are allowed to resume at a later point during assessment day.

**Table 2. T0002:** Measures used for the assessments on different time points.

	Pre-intervention	Post-intervention	
	T0	T1	T2
Demographic data	x		
Sleep diary	x	x	x
MCTQ	x		
PSQI	x	x	x
LEC-5	x		
PCL-5	x	x	x
PCTI	x	x	x
CTQ	x		
BDI-II	x	x	x
BAI	x	x	x
WHODAS 2.0	x	x	x

Abbreviations: *BAI*, Beck Anxiety Inventory; *BDI-II*, Beck-Depressions-Inventar; *CTQ*, Child Trauma Questionnaire; *LEC-5*, Life Events Checklist for DSM-5; *MCTQ*, Munich ChronoType Questionnaire; *PCL-5*, PTSD Checklist for DSM-5; *PCTI*, Post-traumatic Cognitions Inventory; *PSQI*, Pittsburgh Sleep Quality Index; *WHODAS 2.0*, WHO Disability Assessment Schedule.

x, Instrument is assessed at respective timepoint.

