### Statistical analysis

2.9.

Statistical analyses will be based on a mixed general linear model design with the two-level between group factor intervention (intervention vs. control group) and the three-level within group factor time (assessments at T0, T1 and T2) for primary and secondary outcome measures to account for both hypotheses tested in this study. A multilevel approach including study centers with their, presumably, differing TAU interventions, is not feasible due to too low a number of study centers at this hierarchical level. However, as discussed below, study centre and TAU interventions will be used as covariates and for exploratory analyses. For the first research question, the interaction between groups and time will be analysed to determine whether PTSD symptom severity differs for the intervention group after receiving the add-on treatment. For the second research questions, sleep disturbance before the intervention will be used to predict PTSD symptom severity at first and second follow-up for both groups. Due to the exploratory nature of this study, analysis will be conducted both with an intention-to-treat and a per-protocol approach, allowing for a comparison of both effect estimates (Gupta, 2011). For intention-to-treat analysis, dropouts will be included with a last observation carried forward strategy. Extreme cases and outliers will be checked for validity and excluded for per-protocol analysis if indicated. Dropouts will be reported with time point and reason in the final results. We intend to include age, gender, severity of trauma (indicated by classification in type-1 and -2 traumata), number of previous traumatic events, content of trauma-related outpatient treatment sessions and recruiting centre as covariates and in further exploratory analyses. Despite our efforts to proactively reduce variance in trauma treatment among participating trauma centers by organizing joint supervisions, we assume there will be left some significant variance that has to be considered in the statistical analyses. The content of trauma-related outpatient treatment sessions will be classified into trauma-focused versus non-trauma-focused therapy elements since it has been shown that in symptomatic acutely traumatized individuals this may cause a significant difference in treatment outcome (Roberts et al., 2019). Furthermore, we will survey whether sleep interventions have been included in the therapy process or not. By this, we intend to control for the most relevant confounding factors arising from between-participant-treatment-differences.

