One issue, however, inherent to the exploratory nature of the study, is that it is yet unknown, how the specific population of acutely traumatized individuals will react to the CBT-I intervention. There might be unexpected side effects or increased adversity of known CBT-I side effects such as initially increased tiredness during daytime after sleep restriction (Kyle et al., 2011). However, studies using sleep interventions in patients with chronic PTSD do not support this notion (Colvonen et al., 2019; Talbot et al., 2014). Importantly, such side effects will be monitored at T1, patients continue to be seen at the acute trauma clinics and can always seek any additional psychotherapeutic or pharmacological assistance (except for benzodiazepines) that they might need within study protocol. Additionally, the study team is available in case participants have any questions or wish to report adverse events.

There also are some considerations arising from balancing the methodological rigor and the explorative nature of this study. As mentioned before, TAU is likely going to vary across study centers, therapists and a heterogeneous population of patients and therefore needs to be controlled for both by randomization as well as assessment and later use of covariates. While this approach does indeed introduce more variance than in a completely controlled study protocol, it can also be considered a strength of this explorative study. The ‘real-world’ context actually provides a much stronger trial for a novel intervention and will render any potential effects of the CBT-I intervention more meaningful. It might even indicate which other interventions CBT-I is best paired with. The issue of using a multicentre approach in this study can be reflected upon with a similar argument. It will assure wider (e.g. geographical) participation, and therefore greater generalizability and representativeness of results.

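### Treatment-as-usual content, recorded around T1 after randomization, is planned as a covariate to control confounding; this can bias the randomized effect in either direction

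*Protocol article*

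**What the plan says.** The Statistical analysis section names realised TAU as a covariate twice. It first says "study centre and TAU interventions will be used as covariates and for exploratory analyses". Its covariate list then contains "number of previous traumatic events, content of trauma-related outpatient treatment sessions and recruiting centre as covariates and in further exploratory analyses". In both places exploratory use is added to covariate use and does not replace it. Session content is to be classed as trauma-focused or not, and the plan will also survey whether TAU included sleep interventions. The stated purpose is: "we intend to control for the most relevant confounding factors arising from between-participant-treatment-differences". The Discussion repeats that TAU variation is to be handled by randomization and by later use of covariates.

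On timing, the Procedure and assessment section says that "participants will provide written informed consent and are randomized to one of the two study conditions", after which the T0 questionnaire is sent. Session content comes from a "phone interview around T1 to gather information about current medication, number, and content of trauma-related outpatient treatment sessions". The Treatments/interventions section agrees: "TAU may differ between participants and will be recorded at T1 after the sleep intervention is completed".

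On freedom of treatment, the same section says participants "are free to use any form of treatment that is offered to them". The Discussion adds that patients "can always seek any additional psychotherapeutic or pharmacological assistance", with benzodiazepines excepted.

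Two statements pull the other way. The Trial design section blinds TAU therapists to arm. The Treatments/interventions section mentions TAU differences only in connection with exploratory analysis.

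**The concern.** The plan treats TAU content as a confounder. In a randomized comparison, causes of TAU content that exist before allocation are balanced in expectation. What remains in realised content is partly a possible consequence of allocation.

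The article itself supplies the route. Its Background cites a guideline that ties early trauma-focused CBT to clinical symptoms and monitoring to subclinical symptoms. The intervention is meant to change those symptoms. The Statistical analysis section says that trauma-focused content may make a significant difference to outcome. So arm may change symptoms, symptoms may change content, and content may change later symptoms. TAU sleep elements can follow the same route, since a patient whose insomnia improves with the app may need fewer of them.

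The research question is whether dCBT-I added to TAU reduces trauma-related symptoms. That is a total effect, including whatever the arm does to the rest of care. An analysis that holds TAU content fixed answers a different question, and the reader would not see the substitution.

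**Working it through.** **1. Timing.** The order in Procedure and assessment is: consent and randomization, T0, about 8 weeks of intervention, T1 at 10 weeks, phone interview around T1. TAU content is therefore a post-randomization variable. Age, gender, centre, trauma type and number of previous traumatic events are not.

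**2. The plan's own figure.** N = 86 rests on f = 0.25, α = 5% and power 80% for a between-factor effect. With three visits and an assumed correlation of 0.5 (the article gives none), λ = f²·N·m/(1 + (m−1)ρ) = 0.0625 × 86 × 3/2 = 8.06, and power is 0.801. The figure reproduces. It contains no covariates, so nothing below changes it. For two groups d = 2f = 0.50, used next.

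**3. Where the covariate can do harm.** Let M be trauma-focused content (0/1), constant over visits.
- *Main effect only.* The model contains a term γM at every visit. In the change from T0 this term cancels, so group-by-time does not move in balanced data. In a three-visit random-intercept check with 4,000 participants, the T1 interaction was −0.514 both without M and with M as a main effect.
- *Crossed with time.* This amounts to regressing the change from T0 on arm and M, and the estimate can move.
- *Models of T1, T2 or probable PTSD.* Nothing cancels, so the estimate can move.

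The article does not say which form applies.

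**4. Size if content follows symptoms and has no effect of its own.** Assumptions: true effect −0.50 SD at T1 and T2; visit correlation 0.5; P(M) = logit⁻¹(g × T1 severity); M crossed with time; 2,000,000 simulated participants.

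| g per SD | M, control | M, dCBT-I | T1 unadjusted | T1 adjusted | Loss |
|---|---|---|---|---|---|
| 0.5 | 50% | 44% | −0.497 | −0.483 | 3% |
| 0.8 | 50% | 41% | −0.500 | −0.470 | 6% |
| 1.2 | 50% | 39% | −0.499 | −0.445 | 11% |

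T2 was unchanged in every row.

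**5. Size if content also lowers symptoms by 0.5 SD (assumed).** Total effect = direct effect + (effect of M) × (arm difference in P(M)).
- Shares 50.0% and 44.1%: −0.50 + (−0.5)(−0.059) = −0.4705. The adjusted estimate is about −0.50, an overstatement of 0.0295/0.4705 = 6%.
- Shares 50.0% and 38.6%: −0.50 + (−0.5)(−0.114) = −0.443. The overstatement is 0.057/0.443 = 13%.

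These values apply at T1 if content was settled by symptoms earlier in the intervention phase. If the T1 score itself drives content, steps 4 and 5 largely offset each other at T1 (net overstatement 1% to 3% in the simulation), and the 6% to 13% appears at T2.

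**6. Direction and null case.** If dCBT-I raised the share with trauma-focused content by 10 points, the total effect would be −0.50 − 0.05 = −0.55 and the adjusted one would stay near −0.50, an understatement. If the arm does not shift content, both are −0.50.

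**The case against.** The strongest defence is that the harm is conditional. The test named for the first research question is group-by-time. A time-constant covariate entered as a main effect leaves it alone, and last observation carried forward keeps the intention-to-treat data balanced. Therapists are blind, and patients are approached at the start of treatment, so content may largely follow clinic practice. The article calls the study an exploratory pilot, words the covariate list as an intention, and elsewhere mentions only exploratory use of TAU differences. Final model specification may sit in a fuller document.

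Most of this limits the size. It does not remove the point. Blinding closes the route through the therapist's knowledge of arm. It does not close patient choice or symptom-driven change in therapy. The exploratory-only sentence is outweighed by two covariate statements in the analysis section and a third in the Discussion; at best the article is inconsistent. The purpose given, control of confounding, is wrong for this variable under any model form.

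A reader might infer three stronger things that the documents do not support:
- *That the planned test is certainly biased.* It is not if content is independent of arm, or if the covariate enters only as a main effect in balanced data.
- *That a larger loss, obtained by regressing a single-visit score on arm and content, applies to the main test.* That regression is not the planned group-by-time comparison.
- *That baseline PCL-5 is wrongly left out of the covariate list.* T0 is already a level of the time factor.

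**Conclusion.** The point holds as a risk built into a stated analysis rule. A variable recorded after allocation is to be used as a covariate in the models for the randomized effect, under a confounding rationale that does not apply to it. The same appears to be intended for TAU sleep elements, though the article says only that these will be surveyed as part of that control.

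The distortion needs two conditions: the arm shifts TAU content, and the covariate is crossed with time or enters a model of the T1, T2 or binary PCL-5 outcome. With a direct effect of d = 0.5 it is then about 3% to 13% of the randomized effect at T1, towards or away from zero according to mechanism. The range rests on assumed links between severity and content, an assumed content effect of 0 or 0.5 SD and an assumed visit correlation of 0.5. The article gives none of these. No size was calculated for the binary outcome.

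**What to change.** In the Statistical analysis section, restrict covariates in the main group-by-time and binary PCL-5 analyses to variables fixed before randomization: age, gender, recruiting centre, trauma type and number of previous traumatic events. Remove session content and TAU sleep elements from that list and drop the confounding rationale for them. Report both descriptively by arm, since they may be consequences of allocation, and model them only in analyses labelled exploratory or mediation. Bring the Discussion into line; the Treatments/interventions section already reads this way.

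The cost is wording only. Data collection, the phone interview, N = 86 and the recruitment target of 104 are unaffected.

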
## Discussion

3.

In this study protocol, we describe an RCT trial using a CBT-I intervention delivered via app as an add-on to TAU in a multicentre study. It is designed to explore (i) if an early sleep intervention can reduce sleep disturbances and trauma-related symptoms in patients with acute trauma and (ii) if severity of sleep disturbances before the intervention predicts the development of PTSD symptoms later on. The choice of using an RCT design with the intervention being an add-on to TAU strikes the balance between methodological rigor and the explorative nature of this study wanting to ensure patients receive the treatment they individually need in a naturalistic setting. As far as the authors know, this is the first trial using this type of intervention in acutely traumatized individuals. It has the potential to shed light on the role of sleep and sleep disturbances in acute trauma and may provide a new and easily to administer early intervention. Thereby, it covers an approach that has been suggested in recent review articles (Azza et al., 2020; Swift et al., 2022).

We believe this study has several strengths. A major one is the strong theoretical framework connecting the cognitive and emotional processes after a traumatic event, sleep and CBT-I. With the early implementation of CBT-I the memory consolidation and emotional processing properties of healthy sleep can be utilized at a time in post-traumatic symptom development, when maladaptive processing of the traumatic event might have already started but is not yet manifested. Another advantage of the early intervention is, that it has the potential to prevent not only manifestation of trauma-related symptoms and the associated suffering, but it could even help to save costs for healthcare and workdays lost.

One issue, however, inherent to the exploratory nature of the study, is that it is yet unknown, how the specific population of acutely traumatized individuals will react to the CBT-I intervention. There might be unexpected side effects or increased adversity of known CBT-I side effects such as initially increased tiredness during daytime after sleep restriction (Kyle et al., 2011). However, studies using sleep interventions in patients with chronic PTSD do not support this notion (Colvonen et al., 2019; Talbot et al., 2014). Importantly, such side effects will be monitored at T1, patients continue to be seen at the acute trauma clinics and can always seek any additional psychotherapeutic or pharmacological assistance (except for benzodiazepines) that they might need within study protocol. Additionally, the study team is available in case participants have any questions or wish to report adverse events.

There also are some considerations arising from balancing the methodological rigor and the explorative nature of this study. As mentioned before, TAU is likely going to vary across study centers, therapists and a heterogeneous population of patients and therefore needs to be controlled for both by randomization as well as assessment and later use of covariates. While this approach does indeed introduce more variance than in a completely controlled study protocol, it can also be considered a strength of this explorative study. The ‘real-world’ context actually provides a much stronger trial for a novel intervention and will render any potential effects of the CBT-I intervention more meaningful. It might even indicate which other interventions CBT-I is best paired with. The issue of using a multicentre approach in this study can be reflected upon with a similar argument. It will assure wider (e.g. geographical) participation, and therefore greater generalizability and representativeness of results.

Apart from considerations around the study design, there are some methodological limitations. First, the sleep intervention being delivered in digital format forces the participants to process the intervention content self-reliantly. This may lead to decreased compliance compared to in-person interventions, where therapists can directly address compliance. As we have access to app use and sleep diary data however, we are able to measure participation in the intervention and control group. Second, and related to patient compliance is the self-selection of more motivated and possibly also less severely impaired patients in the CBT-I group. To take this into account we will conduct an intent-to-treat analysis, and we will analyse characteristics of all dropouts to detect potential differences between both groups. Third, beside of sleep questionnaires indicating subjective sleep quality we decided to not include any objective sleep measurements. Thus, changes in sleep architecture that might be related to potential changes in trauma processing cannot be detected. For this first exploratory study, it is more important for us to include a high number of patients at different centres within a reasonable period of time to uncover possible effects of CBT-I at the behavioural level. If this approach is successful, objective sleep data should also be collected in subsequent studies to investigate underlying mechanisms.

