### Sample size

2.4.

The planned sample size is based on calculations in G*Power 3.1.9.7 (Faul et al., 2007). Literature investigating the effect of combined sleep- and trauma-focused therapy on trauma-related symptoms is scarce. Pigeon et al. (2022) report a medium sized effect of CBT-I on trauma-related symptoms measured with the Clinician Administered PTSD Scale (CAPS; Blake et al., 1995) in individuals diagnosed with PTSD after having experienced a traumatic event within the past year. Referring to this finding and being interested in a clinically relevant effect, we chose an effect size of Cohen's *f* = .25 as a basis for power analysis and sample size calculation. Calculations setting the desired power to 80% and the risk of Type I error rate to *α* = 5% resulted in a required sample size of *N* = 86 to be able to detect medium sized between factor effects in a mixed design, provided the assumed effects exists in the investigated population. Considering a dropout rate of 20% from guideline-recommended psychological treatments for post-traumatic stress disorder (Varker et al., 2021) as an orientation for potential attrition rate, we intend to recruit *N* = 52 participants per group. Due to the exploratory nature of this pilot study, we used only our primary outcome measure for sample size calculations.

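### The only scheduled side-effect assessment described is at T1, 10 weeks after baseline, although the side effect the protocol itself names is an initial one; the week-5 call is not described as asking about harms.

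*Protocol article*

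**What the plan says.** Section 3 (Discussion) of the protocol article raises possible side effects in this new population and refers to "known CBT-I side effects such as initially increased tiredness during daytime after sleep restriction". It then says that "such side effects will be monitored at T1" and that contact with the trauma clinics continues. The same paragraph adds that participants can seek further help and can report adverse events to the study team.

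Section 2.7 fixes the timing of T1: "After the intervention phase (10 weeks post baseline), all participants will receive a link to a second online assessment (timepoint T1"). It also describes one contact during the intervention, five weeks after its start: "participants will receive a phone call to encourage compliance and spot potential issues with the use of the app or sleep diary". The phone interview around T1 is described as covering medication and the number and content of outpatient sessions. Table 2 lists no side-effect measure at any time point.

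Section 2.9 says that dropouts will be reported with time point and reason.

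**The concern.** The stated assessment time does not fit the stated risk. The one harm given as an example begins when sleep restriction begins and is expected to fade, yet the scheduled enquiry comes after the programme has finished. A transient effect must then be recalled over several weeks, by someone whose sleep and daytime state have since changed for other reasons, including the trauma itself and usual treatment.

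Participants who leave before T1 have no scheduled harms enquiry at all. If leaving is related to a side effect, the rate among those who answer at T1 is too low.

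The Discussion presents the trial as the first of its kind in acutely traumatised people and as a possible basis for an easily delivered early intervention. A usable comparison of side effects between arms is part of what later users will want from it. Tiredness is also common in untreated insomnia and after trauma, so a count is informative only if both arms are asked the same questions at the same times.

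**Working it through.** The plan states no figure for harms, so there is none to reproduce. The check sets the timeline out and then asks how far the size of the gap can be pinned down.

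**1. Timeline** (sections 2.6.1, 2.7 and 2.8.2)

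- Intervention: about 8 weeks, starting after baseline. The pre-intervention diary fills the week before the start and the post-intervention diary the week after the end, so 1 + 8 + 1 = 10 weeks agrees with T1 at 10 weeks.
- The start is therefore 0 to 1 week after baseline, and T1 falls 9 to 10 weeks after the start. The call comes 5 weeks after the start.

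**2. When would early tiredness arise?** The side effect is tied to sleep restriction, not to the first day of app use. Table 1 lists sleep restriction in the sixth entry (sleeping hours) and bases the sleep window on the last 7 days of diary. The pace through the modules is not stated, so two assumed cases are shown:

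| Assumed start of sleep restriction | Weeks back from T1 | Weeks back from the call |
|---|---|---|
| Week 1 (as soon as 7 diary days exist) | 9 − 1 = 8 to 10 − 1 = 9 | 5 − 1 = 4 |
| Week 4 (10 core modules spread evenly, five done: 5/10 × 8) | 9 − 4 = 5 to 10 − 4 = 6 | 5 − 4 = 1 |

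The call is 4 to 5 weeks closer to the expected effect than T1. For anyone who reaches sleep restriction after week 5 the call is too early, which is why T1 must stay.

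**3. Which contacts could record a harm before T1?**

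| Contact | What is described | Harms asked about? |
|---|---|---|
| Week-5 call (2.7) | Compliance; issues with use of app or diary | Not named |
| Clinic visits (3) | Usual treatment continues | No route to the study record described; therapists are blind to arm (2.1) |
| Study team (3) | Available to those who wish to report adverse events | Only on the participant's initiative |
| Dropout record (2.9) | Time point and reason | Only if given as the reason |

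**4. How many might lack a T1 answer?** Section 2.4 uses 20% dropout and 52 per arm. If all of that loss fell before T1, 0.20 × 52 = 10.4 per arm would give no T1 answer. This is an orientation figure for attrition, not a T1 non-response rate. At an assumed 10% the number is 5.2. The 68% app completion rate in section 2.6.1 would leave 0.32 × 52 = 16.6, but stopping the app is not the same as missing T1.

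**5. Can the under-recording be sized?** Let d be the share lost before T1, r the share of early effects recalled at T1 and s the share reported spontaneously. If dropouts and completers have the same risk:

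captured share = (1 − d) × [r + (1 − r) × s] + d × s

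| d | r = 0.5, s = 0 | r = 1, s = 0.5 |
|---|---|---|
| 0.10 | 0.90 × 0.5 = 0.45 | 0.90 × 1 + 0.10 × 0.5 = 0.95 |
| 0.20 | 0.80 × 0.5 = 0.40 | 0.80 × 1 + 0.20 × 0.5 = 0.90 |
| 0.32 | 0.68 × 0.5 = 0.34 | 0.68 × 1 + 0.32 × 0.5 = 0.84 |

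All values of r and s are assumptions, and the result runs from 0.34 to 0.95. With equal risk, loss before T1 lowers the count of cases but does not bias the rate among those assessed; that bias needs dropout to be related to harm, on which the document is silent.

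**The case against.** The strongest reply is that harms are not confined to T1. The sentence about T1 goes on to continued clinic contact and further help, and the next one offers adverse-event reporting at any time. The week-5 call looks for issues with using the app, and sleep restriction is app content, so tiredness may well come up. The T1 link and the T1 phone contact go to all participants, including those who have stopped the app. Dropout reasons are recorded. The Discussion also notes that studies of sleep interventions in chronic PTSD do not support a worse side-effect burden. Finally, this is a condensed article: harms instruments and adverse-event procedures usually sit in the full protocol, and the trial's stated aims are efficacy and prediction.

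Much of this stands, and it rules out four stronger readings that a reader might infer:

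- That side effects can be recorded only at T1. This is true only of scheduled, active assessment.
- That the study team cannot hear of a harm while the intervention is running. The open reporting route and the call both contradict this.
- That a fifth of app users will have no side-effect record. The 20% is borrowed from psychological treatments for PTSD as a guide for sample size, and it is not tied to T1.
- That the recorded rate will be too low by a known amount. No input for such a figure is in the document.

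The mismatch in timing survives. The absence of a named instrument is no fault in an article, but the article does fix when side effects are monitored, and that time is after the expected effect. Spontaneous reporting narrows the gap without closing it, since tiredness that passes, or that is put down to the trauma, is easily left unmentioned.

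**Conclusion.** The point holds as a mismatch between the harm the protocol expects and the only time at which it describes asking about it. Early and transient side effects are likely to be under-recorded, and participants lost before T1 have no scheduled harms enquiry. Likely is the right word: the direction follows from reliance on recall and on participants' own initiative, but the amount depends on recall, reporting and loss rates that the document does not give.

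The conclusion assumes that the article describes the harms schedule as it will be run. If the full protocol already has side-effect questions in the week-5 call and at withdrawal, only the sentence in the Discussion needs correcting. The primary analysis and the sample size are untouched. This is a worthwhile, low-cost improvement to the tolerability record of a first trial in this population.

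**What to change.** - Write a short, standard set of side-effect questions, including daytime tiredness, with the same wording for both arms.
- Ask them at the existing week-5 call, keep the T1 assessment, and ask them again whenever a dropout reason is recorded.
- At the week-5 call, note for app users whether sleep restriction has begun, so that answers given before and after it can be told apart.
- Report results by arm, with the number assessed at each point.
- Amend section 2.7 and the Discussion so that both give the same schedule.

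The cost is a few extra minutes per call and, for participants who withdraw, a few questions at a contact that is in any case needed to obtain the reason. No extra visit or staff is required. There are two limits. Section 2.5 says that study conductors are not blind, so the questions should be read from a fixed script to limit differential probing. A week-5 question also still relies on recall, over about 1 to 4 weeks in the cases shown, and so reduces the problem without removing it. The change concerns measurement only and alters no treatment rule.
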